### Definitions

In this study, we define complete abortion as when no signs of pregnancy or retention of product of conception (POC) is present, or upon a negative LSUP test, and no further treatment is needed for termination of the pregnancy. We define incomplete abortion as partially retained POC, sometimes with an enlarged size of the uterus or a positive LSUP test. Incomplete abortion requires further treatment, preferably with additional misoprostol or manual vacuum aspiration (MVA). We define on-going pregnancy as persistent pregnancy symptoms, no POC expulsion and enlargement of the uterus
[19]. Moreover, with the LSUP-test we are referring to the combined low- and high- sensitivity pregnancy test purchased from VEDA.LAB (http://www.vedalab.com). The high-sensitivity component is equal to a standard pregnancy test and has a sensitivity of 5 units/litre. The low-sensitivity component has a sensitivity of 1000 units/litre, and is suitable for the use to assess abortion outcome at 10–14 days post abortion. In this study, the low-sensitivity component is of interest, however since there are no separate LSUP tests available on the market we used the combined test. Moreover, the test used in this study is not available in India, however several international pregnancy test manufacturers are currently working to develop LSUP-tests, and its availability on the market is likely to increase in the near future.

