### Sample size

The success rate of medical abortion is 95%
[31,32] resulting in a complication rate estimation of 5% in both groups. The primary outcome define the sample size estimation where the 5% non-inferiority margin (delta) establishes the non-inferiority of the home-based self-assessment following medical abortion as compared to the routine clinic follow-up. The delta margin is defined by the clinical assessment standpoint where a 5% difference does not have clinical importance. To proof the non-inferiority of the intervention at a significance level of α = 0,05 and a power of 80%, 596 women are needed. The lost to follow-up estimation of 20%, based on field-testing in the study area, resulted in a final sample size of 716 women. A two-sided 95% confidence interval (CI) (or a one-sided 97,5% CI) will determine the difference in percentage of women requiring surgical intervention from the two groups.

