### Primary study outcome

*The primary outcome* of the study is the rate of complete abortion, when no signs of pregnancy or retention of POC is present, or upon a negative LSUP test, and no further treatment is needed for termination of the pregnancy, in both groups. Established classification of efficacy for medical abortion will be followed to determine the outcome of the abortion procedure
[22,35]. Hence the primary outcome is; efficacy of home-based assessment, measured as the rate of complete abortion, relative to routine follow up at two weeks after initiation of medical abortion. The failed abortion rate will be measured through number of surgical interventions, clinical administration of additional misoprostol or on-going pregnancies established upon clinical examination.

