### Data analysis

SPSS 20.0 will be used for statistical analysis. All analyses will be by intention to treat (ITT) and some will be analysed using per protocol analysis in addition to ITT. The non-inferiority hypothesis will be tested at a significance level of 5% (α = 0,05). Categorical outcomes will be presented using descriptive statistics and compared using χ^2^-test. Numerical variables will be assessed for significance using the student’s t-test. Intergroup comparison will be made between the clinic follow-up group and the home-based assessment group. Differences between groups will be analysed using relative risks (95% CI) and logistic regression for the relative differences. P-values equal to or lower than 0.05 will be considered statistically significant. Acceptability measures will be analysed descriptively, using numbers and percentages of women in the different categories.

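### The stated 95% confidence interval is for surgical intervention alone, while the 5-point margin and the sample size belong to complete abortion

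*Protocol article*

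**What the plan says.** **Primary study outcome.** The main endpoint "of the study is the rate of complete abortion, when no signs of pregnancy or retention of POC is present"; a negative low-sensitivity test also qualifies, and there must be no need of further treatment. Failure has three components: it is "measured through number of surgical interventions, clinical administration of additional misoprostol or on-going pregnancies established upon clinical examination".

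**Sample size.** Success of 95% is assumed, "resulting in a complication rate estimation of 5% in both groups". The section says that the primary outcome drives the calculation and that the margin is 5%. With α = 0.05 and 80% power it arrives at 596 women. It then specifies a two-sided 95% interval, equivalently one-sided 97.5%, which "will determine the difference in percentage of women requiring surgical intervention from the two groups".

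**Data analysis.** "The non-inferiority hypothesis will be tested at a significance level of 5" per cent. No endpoint, margin or interval is attached to that sentence. The methods named are a χ² test, a t-test and the following: "Differences between groups will be analysed using relative risks (95% CI) and logistic regression for the relative differences".

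**Discussion.** The sample size is again described as resting on complete abortion at 95%, with 298 evaluated women needed in each group.

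**The concern.** The margin and the interval compared with it should refer to the same endpoint. Here the margin was set for all failures (5% expected), but the only interval on the absolute-difference scale in the article is for surgery.

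The two endpoints differ in this trial. The Definitions section allows incomplete abortion to be treated with additional misoprostol as well as by manual vacuum aspiration, so a woman can fail on the primary outcome without surgery. An on-going pregnancy established at clinical examination is also a failure in its own right.

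If the surgical interval were used as the decision rule, an excess of non-surgical failures in the home-based group would not count against the margin. Leaving two candidate endpoints in the text also allows a choice between them after the results are known.

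**Working it through.** **1. Reproduce the plan's figure.** Inputs from Sample size: success 0.95 in both groups, margin 0.05, one-sided α 0.025 (from the two-sided 95% interval), power 80%.

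n per group = [p(1−p) + p(1−p)] × (z₀.₉₇₅ + z₀.₈₀)² / δ²
= 2 × 0.95 × 0.05 × (1.960 + 0.842)² / 0.05²
= 0.095 × 7.849 / 0.0025 = 298.3

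This agrees with the 298 per group in the Discussion and 596 in total (rounding up would give 299 and 598). The plan's number is therefore the one for a 95% interval on overall failure at 5%, the complement of complete abortion.

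**2. Compare the endpoints.**

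| Place | Endpoint used |
|---|---|
| Primary study outcome | Complete abortion; failure = surgery, additional misoprostol or on-going pregnancy |
| Sample size, assumptions and margin | Primary outcome, 95% success |
| Sample size, last sentence (the interval) | Surgery only |
| Data analysis, non-inferiority sentence | None stated |
| Discussion, sample size | Complete abortion, 95% |

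Only the interval sentence departs from the rest.

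**3. What the surgical interval would do.** Take the boundary case in which home-based assessment is worse by the whole margin: failure 10% (home) against 5% (clinic), 298 per group. Let a share f of failures be surgical in both groups. The article gives no surgical rate, so f is assumed and varied. The surgical rates are then 0.10f and 0.05f, and the true surgical difference is 0.05f.

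Approximate chance that the upper 95% limit for surgery lies below 5 points:

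Φ[(0.05 − 0.05f)/SE − 1.960], with SE = √[0.05f(1−0.05f)/298 + 0.10f(1−0.10f)/298]

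For f = 0.6: SE = √[(0.03 × 0.97 + 0.06 × 0.94)/298] = 0.0169; (0.05 − 0.03)/0.0169 = 1.18; Φ(1.18 − 1.96) = 0.22.

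The exact column sums the binomial probabilities of all outcomes in which the simple (Wald) interval meets the rule.

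| Share surgical (assumed) | Surgery, clinic / home | Approximate | Exact |
|---|---|---|---|
| 100% | 5% / 10% | 2.5% | 2.9% |
| 80% | 4% / 8% | 7% | 8% |
| 60% | 3% / 6% | 22% | 23% |
| 40% | 2% / 4% | 58% | 57% |

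The first row is also the result for an interval on all failures. The 2.9% against a nominal 2.5% is ordinary behaviour of this interval at this sample size and is not part of the problem.

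**4. Effect of the correction.** Moving the interval to complete abortion returns to the calculation in step 1, so 298 per group still gives 80% power.

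**The case against.** The strongest reply is that the intention is plain. Sample size ties the margin to the primary outcome, Primary study outcome frames efficacy as the complete-abortion rate relative to routine follow-up, Data analysis announces a non-inferiority test, and the Discussion repeats the 95% basis. One sentence names another endpoint. A short article may also leave the detail of the test to a fuller document.

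Much of this stands, and it rules out three stronger readings that a reader might infer:

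- *That the plan does not test its primary hypothesis.* This would require treating one sentence as the whole decision rule against the other sections.
- *That the 5% level is ambiguous and might be one-sided.* Sample size settles it by naming the two-sided 95% or one-sided 97.5% interval, and 596 reproduces at one-sided 0.025.
- *That a non-significant χ² test would be taken as non-inferiority.* Data analysis does not say so. It lists χ², relative risk and logistic regression generically, and they can serve the secondary outcomes.

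The reply does not remove the contradiction. The article did not leave the interval to another document: it stated one, on a component of failure. Data analysis does not correct it, because the non-inferiority sentence there has no endpoint or margin.

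The error rates in the working depend on an assumed surgical share, which is a fair criticism. They are given as a range for that reason.

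**Conclusion.** The point holds as an internal contradiction that is wrong as written. The margin and the 596 women belong to complete abortion; the interval is placed on surgery and omits two of the three failure types, and no named method is tied to the margin.

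The consequence is conditional on that interval being used to decide. The chance of a false claim of non-inferiority would then rise from about 2.9% to about 8%, 23% or 57% if 80%, 60% or 40% of failures are surgical. These figures assume true failure of 10% against 5%, 298 evaluated women per group and the same surgical share in both groups. Only if every failure were surgical would the error rate be unaffected.

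**What to change.** In Sample size, replace the endpoint in the last sentence. State that the primary analysis is the difference (home minus clinic) in the proportion with complete abortion as defined in Primary study outcome, with a two-sided 95% confidence interval, and that non-inferiority is concluded if the lower limit lies above −5 percentage points. In Data analysis, refer the non-inferiority sentence to that rule. Report surgical intervention as a secondary outcome.

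The cost is wording in two sections. The sample size is unchanged and no new data are needed, since Primary study outcome already calls for all three failure types. The change should be dated before any comparison of the groups is seen.

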### Research team

In addition to the obstetricians and nurse-midwives already working in each of the study sites, four research assistants (RAs) were assigned to the project. The RAs are women with a bachelor’s degree and a few years of experience working in the study area. They speak the local dialect and are aware of the local traditions and customs. In addition, a research associate for coordination of the study and a data manager to monitor the data entry and to attend to data-entry queries were assigned.

The research team received training before the initiation of the study-related activities and a final orientation will be provided at the time of initiation of data collection. Providers will be included in the orientation at the time of study initiation to create a general on-site understanding of the study. A manual on how to carry out the study and fill in the questionnaire will be available at each study site.

### Adaptation phase

We field-tested the intervention to ensure feasibility and adaptation to the context. This included the evaluation of the LSUP-test procedure and the pictorial instruction sheet explaining how to use the LSUP-test as well as possible danger signs of medical abortion (Figure 
1). The Indian national standard guidelines for comprehensive abortion care and other similar pictorial guidelines used in the context of medical abortion
[11,33] inspired the pictorial instruction sheet used for this study. Women from the designated field area interpreted and explained what they understood from the instruction sheet to validate the content. The pictorial instruction sheet was repeatedly modified and field-tested until it could fully aid women to understand how to use the LSUP-test by themselves, as well as when to return to the clinic in the event of any side effects or complications. While testing the intervention, we also tested and adapted the study questionnaire. This was to ensure a good flow in the questioning and an appropriate way of posting the questions. All questions were translated to the local language and the meaning of content was thoroughly discussed and concluded upon together with clinical staff and RAs. In addition, the obtaining of the informed consent was field-tested, as most participants cannot read the information sheet for themselves. This resulted in RA administered consent taking and a simplification of the text in the consent form, however in accordance with ethical committee guidelines.

**Figure 1 F1:**
[figure not shown]
**The pictorial instruction sheet used for the home-based assessment group.** The instruction for use and interpretation of the LSUP-test (left side) and the pictorial explanation of the danger signs that may occur after a medical abortion indicating that the woman need to return to the clinic or consult a health care provider (right side). The pictorial instruction sheet consists of both pictures and text to cater to the different needs and literacy levels of the inhabitants in this setting.

The study procedures of the intervention group were field tested in the clinics of ARTH, during October and November 2012. We assigned all eligible women that agreed to participate to the home-based assessment intervention to carry out the LSUP-test (n = 33). At the time of follow-up the RAs interviewed the women regarding how much the woman had understood of the informed consent, the LSUP-test procedure and whether she felt safe about participating in the study. The responses from the women gave an understanding of the feasibility of the study protocol and the home-based assessment procedure as well as the accuracy of the questions in the questionnaire.

When assessing means of follow-up we found that majority of rural women required home-visits, largely due to the lack of personal ownership of cell-phones and hence confidentiality. To maintain the confidentiality of the women at the time of the home-visit the researchers adopted techniques such as camouflage visits to other women in the village, women of reproductive age commonly with recently born babies or women that were pregnant. In addition, in case any other family member or neighbour came in to the room of the interview, the RA immediately altered the topic of conversation. If complete privacy could not be obtained during the interview the RA would come back at another time, alternatively meet the woman elsewhere at her convenience e.g. by the water pump or in her farm. In the cases of a positive LSUP test or the presence of any danger signs, routes of referral and follow-up needed to be tested and streamlined. In addition to these adjustments, the routine of providing a contraceptive method at the time of follow-up needed alteration in the home-based assessment group since they no longer presented in the clinic. Discussions with the research staff about limiting loss of contraceptive uptake resulted in an updated clinic guideline where contraceptive counselling and provision, where applicable, was provided at the time of the first encounter or at the time of clinic administration of misoprostol.

Once the home-based assessment group was field tested, and the questionnaires and the pictorial instruction sheet finalized, we initiated a field test of the clinic follow-up procedure (n = 36). The clinic follow-up group followed the clinic protocol with two to three clinical visits in total. Instead of routine follow-up at seven days post abortion the follow-up occurred at 10–14 days post initiation of the medical abortion for the purpose of the study as well as to avoid over-diagnosis of incomplete abortions. Previous experience from service provision in this field area indicates that a large proportion of women do not return for clinic follow-up after an abortion. This affects the outcome as well as the validity of the study, which is why additional efforts were put into finding means of retaining the women in the study. Reasons why women would not return for the clinical follow-up were explored, and it was found that lack of transport and loss of income were major contributors to the drop-out. Provision of financial reimbursement for transport costs was tested and proved efficient in enhancing successful clinic follow-up. In addition, women mentioned lack of time as a reason for not returning to the clinic unless they suffered from any complications.

### Randomisation procedure

The randomisation list will be generated using a computerized random number generator (random allocation software 2.0
[34]). The staff generating the list and preparing the opaque sealed envelopes are not to be involved in any data collection. The randomisation procedure is visualised in the flowchart (Figure 
2). Randomization of the study participants will occur after the first clinical encounter with the doctor. Subsequently, the service provision will occur in a uniform and standard manner regardless of group allocation or study participation. Further blinding is not possible since the means of follow-up are depending on the group allocation. The clinical procedure on day one and three will remain the same regardless of group allocation of the woman. However, the location of misoprostol administration on day three, at home or in the clinic, is agreed upon based on the providers’ assessment together with the woman’s preference. Thus, this decision is made before the enrolment in the study. Block randomisation will be applied to ensure equal distribution of the two study groups in each clinic. Each clinic will be provided with envelopes according to their caseload. Consequently, the number of study participants will vary in each clinic.

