### Study setting

ARTH, a not for profit public health organisation, operates three rural and one urban clinic in and around Udaipur in the southern part of Rajasthan state in India. ARTH’s three rural clinics cater to women living in an area characterized by poor road connections, poverty, and low literacy among women (48.5%). The women in this area belong to different social groups, where about half the population belong to the marginalized groups, scheduled caste or scheduled tribe. Apart from carrying out domestic work, women in this area are largely engaged in marginal farming, wage labour and animal husbandry. In contrast to the rural clinics, ARTH’s urban clinic caters to a wider range of women, however majority from a low socioeconomic stratum. The services were made available at the ARTH clinics at a cost to the use of about 4 USD equivalent. To increase the urban sample, we approached two private nursing homes known to provide medical abortion in the city of Udaipur to act as study sites. Their services, subsidized for the purpose of the study, range between 6.5 and 16 USD. In total six clinics, three urban and three rural clinics were included as study sites. Approximately 550 women receive MTP from ARTH’s health centres annually, and of these about 450 women opt for medical abortion. The summarized caseload of the private clinics is an estimated 100 medical abortions per year. Home administration of misoprostol accounts for about 40% of all medical abortions.

Inclusion criteria:

–Women with unwanted pregnancies, who opt for medical abortion at any of the six above described study sites.

–Gestational age of less than or equal to nine weeks, as assessed by an obstetrician.

–Residing within the identified study area consisting of 70 villages in a range of 25 km from the rural clinics (at the rural clinics only).

–Agree to follow-up after 12–15 days, by either phone or home-visit.

Exclusion criteria:

–Women with known contraindications to medical abortion, as assessed by the doctor

–Haemoglobin-value less than 8.5 g/l.

–Younger than 18 years

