#### Follow-up of clinic follow-up group on day 10–14

Women allocated to the clinic follow-up group will be treated according to the routine practice of each clinic. For the cause of the study the time of the follow-up visit has been standardized to 14 days after initiation of medical abortion, or within the range of 10–14 days. At the follow-up visit, a doctor will assess the outcome of the abortion including a pelvic examination if regarded as necessary. Subsequently, an RA will carry out the final interview in the clinic before the woman will be censored out of the study. Women returning to the clinic will be reimbursed for their travel expenses (INR 200), while women that do not return for clinical follow-up will be reminded to return to the clinic over phone, where possible.

All women

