## Discussion

This paper summarizes the implementation and administration of an RCT that seek to test the feasibility and efficacy of home-based assessment after an early medical abortion using an LSUP-test and a pictorial instruction sheet. The intervention is designed to accommodate disadvantaged women living in remote as well as urban areas of India. This paper describes the study protocol of an RCT along with the course of adaptation and implementation of the study-intervention.

To increase generalizability of the results, exclusion criteria are limited to those of clinical importance to maintain the safety of the women. Due to the study design, women attending the rural clinics that are residing outside the defined study area will be considered ineligible. However, the study area includes 70 villages, where each village hosts approximately 10.000 inhabitants, including women from different socio-economic strata and with different educational backgrounds. Moreover, no area restrictions are applied to the women recruited in the urban clinics. Thus the sample will be generalizable. The sample size calculation is based on the likelihood of an early medical abortion resulting in a complete abortion (95%), rather than the likelihood of an on-going pregnancy (1-2%). This may limit the ability to identify the clinically important finding of on-going pregnancy. However, it is the commonly used outcome for trials investigating efficacy and safety of medical abortion due to its high success rate. This has been done similarly in trials by the WHO and Sunde-Oppegard et al. investigating schemes of follow-up after medical abortion
[35]. With the additional assumption of a loss to follow-up of 20% based on the field testing, the total study sample required is 716 women, where 298 women with evaluated end point in each group is required to maintain power.

All recruited RAs have been working in the field under ARTH for several years, in their designated field area. This is considered a benefit, as it will diminish suspicion from neighbours during home visits, ensuring confidentiality of the women in the study.

Wolff argues that to conduct a service effectiveness study it is crucial that the intervention is accurately implemented and consistently operationalized throughout the study
[38]. In addition, this needs to be recorded and described in detail so that it can be replicated elsewhere

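### Randomisation is blocked within six clinics, but the named primary comparisons are unstratified; the effect is small, and stratifying by clinic costs little (minor)

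*Protocol article*

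**What the plan says.** **Allocation.** Randomisation procedure states: "Block randomisation will be applied to ensure equal distribution of the two study groups in each clinic". It adds: "Each clinic will be provided with envelopes according to their caseload", so clinics will contribute unequal numbers. Study setting gives the strata: "In total six clinics, three urban and three rural clinics were included as study sites". The Discussion implies 1:1 allocation: "298 women with evaluated end point in each group is required to maintain power".

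**Analysis.** Sample size plans a two-sided 95% (one-sided 97.5%) confidence interval for the difference in percentages between the groups. Data analysis adds: "Categorical outcomes will be presented using descriptive statistics and compared using" a χ² test; "Intergroup comparison will be made between the clinic follow-up group and the home-based assessment group"; and "Differences between groups will be analysed using relative risks (95% CI) and logistic regression for the relative differences". Neither section names clinic as a stratum or covariate. Neither says that the regression will be unadjusted.

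**Follow-up.** Adaptation phase reports that transport and lost income were major reasons for not returning to the clinic, and that reimbursing travel helped. The Discussion says that clinic-arm follow-up stayed below the home arm even with the incentive, and lists heavy clinic-arm dropout as a possible limitation. The section on additional procedures, extra visits and loss to follow-up provides for tracing lost women by phone or home visit within three months.

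**The concern.** When allocation is restricted within strata, the analysis should normally carry the same strata. Leaving them out has two possible consequences.

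1. **Precision.** The crude variance includes between-clinic variation that blocking has already removed from the treatment contrast, so the interval is a little too wide.
2. **Clinic mix.** Blocking balances the women randomised, not the women evaluated. If clinic-arm losses fall mainly on the sites that are hard to reach, the evaluable arms have different clinic mixes. A crude difference then picks up some of the difference between clinics.

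It is plausible that outcome varies by clinic. Sites are rural or urban and non-profit or private, and observation after misoprostol varies by clinic and practitioner. Failure also depends partly on a provider's decision, because it counts surgical intervention and extra misoprostol. The article gives no outcome rate by clinic.

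**Working it through.** **Inputs from the article.** Success is 95% in both groups, the margin is 5 points, power is 80% and 596 women must be evaluable (Sample size). That is 298 per group (Discussion), in six clinics (Study setting). Clinic success rates, exact clinic shares and loss by site are not given, so those below are assumptions.

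**Step 1: the plan's own figure.** Unstratified non-inferiority formula with one-sided α = 0.025:

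n per group = (1.960 + 0.842)² × 2 × 0.95 × 0.05 / 0.05² = 7.85 × 38 ≈ 298.3

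This is 298 per group or 596 in all as stated, or 598 if rounded up. The calculation takes no account of clinic. The crude standard error is √(2 × 0.0475 / 298) = 1.79 points.

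**Step 2: balance kept within clinics.** If the arms are equal in every clinic, the crude difference equals the clinic-size-weighted average of the within-clinic differences, so it is unbiased. Only the variance differs:

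- Variance ratio R = Σ w_c p_c(1 − p_c) / [p(1 − p)], where w_c is the clinic share and p_c the clinic success rate.
- Crude power = Φ[(0.05 − 1.96 × SE_crude) / SE_within]
- Stratified power = Φ[0.05 / SE_within − 1.96], with SE_within = SE_crude × √R
- Crude one-sided type I error ≈ 1 − Φ(1.96 / √R)

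Assumed shares are 10, 20, 25, 27, 9 and 9%, with overall success held at 95%.

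| Assumed clinic success | R | Power, crude | Power, stratified | Type I error, crude |
|---|---|---|---|---|
| 95% everywhere | 1.000 | 80.0% | 80.0% | 0.0250 |
| about 91–98% | 0.991 | 80.1% | 80.3% | 0.0245 |
| about 84–99% | 0.956 | 80.5% | 81.7% | 0.0225 |

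In 40,000 simulated trials per scenario with Wald intervals, crude and stratified power were 79.9% and 80.6%, 79.9% and 80.8%, and 80.4% and 82.3%. Part of that gap is not real: 0.7 points appear even with identical clinics, because the variance is underestimated in small strata. Simulated type I error was 0.026–0.029 for the crude interval and about 0.029 for the stratified one. The excess over 0.025 is already there with identical clinics, so it comes from the Wald interval with few failures, not from omitting clinic.

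**Step 3: loss that differs by arm and by clinic.** Assume no true effect, half the women at rural sites (3% failure) and half at urban sites (7%). The clinic arm loses 30% of rural and 10% of urban women; the home arm loses 5% of each.

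- Clinic arm: (0.35 × 3% + 0.45 × 7%) / 0.80 = 5.25%
- Home arm: (0.475 × 3% + 0.475 × 7%) / 0.95 = 5.00%
- Crude artefact: 0.25 points towards home, or 0.25 / 1.79 = 0.14 standard errors

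The within-stratum differences are zero, so any stratified estimate is zero.

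Sensitivity to the assumptions:

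- Site rates reversed (rural 7%, urban 3%): (0.35 × 7% + 0.45 × 3%) / 0.80 = 4.75%, so 0.25 points against home.
- Wider site rates (2% and 10%): (0.35 × 2% + 0.45 × 10%) / 0.80 = 6.5% against 6.0%, so 0.5 points.
- Tracing recovers half the clinic-arm losses (15% and 5% lost, rates 3% and 7%): (0.425 × 3% + 0.475 × 7%) / 0.90 = 5.11%, so 0.11 points.

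**Step 4: sparseness.** Expected failures are 0.05 × 596 ≈ 30. Over 6 × 2 = 12 clinic-by-arm cells that averages 2.5 per cell, and fewer in small clinics.

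**The case against.** **The article is silent; it does not reject clinic.** A reader might infer that the trial has decided to ignore clinic in every analysis. The text does not support that. The regression's covariates are unstated and may include clinic, and a condensed article can leave such detail to a fuller plan. What stands is narrower: the interval for the difference, the χ² test and the relative risk, as named, are unstratified. Adjusting a regression meant for relative differences would not change the risk-difference interval on which non-inferiority is judged.

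**The harm is small and need not favour home follow-up.** A reader might infer that the crude analysis inflates type I error or is biased towards non-inferiority. With balance kept, the opposite holds slightly. With unequal loss, the direction depends on unknown site rates. A 30% rural loss is also pessimistic, given that reimbursement was judged to help and that lost women are to be traced.

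**Stratifying does not solve dropout.** The article's main worry is that women return only if they have complications. That is outcome-related loss within a clinic, and stratifying leaves it untouched. This objection stands in full.

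**Clinic practice.** Control women "will be treated according to the routine practice of each clinic", but this describes control-arm follow-up, with its timing standardised. It does not show that care differs by clinic in both arms.

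**The remedy needs care.** With about 30 failures, six clinic effects risk empty cells, so a pooling rule is necessary.

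**Conclusion.** The point holds as a minor one. Allocation is restricted by clinic, and the named primary comparisons do not carry that stratum.

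- With balance kept within clinics, the crude comparison is unbiased and slightly conservative. It costs about 0 to 1 point of power under the assumed clinic differences, and omitting clinic does not raise type I error.
- With loss that differs by arm and clinic, the crude difference could move by roughly 0.1 to 0.5 points in either direction under the assumptions shown. The central illustration, 0.25 points, is one-twentieth of the 5-point margin.

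Both results rest on clinic shares, site failure rates and loss rates that the article does not give. Neither suggests that the trial's conclusion would be invalid, and 596 evaluable women remains essentially the right number for the stated assumptions with either analysis.

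**What to change.** State in the analysis plan, before outcome data are compared by arm, that:

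1. The primary risk difference is estimated stratified by clinic, using Mantel–Haenszel weights and a stratified score (Miettinen–Nurminen) or Newcombe 95% interval. These suit rare failures better than a Wald interval.
2. Small clinics are pooled by a rule fixed beforehand, for example within rural and within urban sites when a clinic falls below a set number of women or failures.
3. The logistic regression includes the same strata.
4. Loss to follow-up is reported by arm and clinic, and outcome-related loss is handled by separate missing-data sensitivity analyses.

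**Cost.** No extra women or data collection are needed, because allocation is organised by clinic. The work is analysis code and a short sparse-cell rule. The statistical downside is small: without pooling, small strata can give empty cells and understated variance.
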